## Abstract

**Background:**

The EUDAIMON study focuses on fibromyalgia syndrome (FMS), a prevalent chronic condition characterized by pain, fatigue, cognitive problems and distress. According to recent reviews and meta-analyses, Mindfulness-Based Stress Reduction (MBSR) is a promising therapeutic approach for patients with FMS. The measurement of biomarkers as part of the analysis of MBSR effects would help to identify the neurobiological underpinnings of MBSR and increase our knowledge of FMS pathophysiology. The main objectives of this 12-month RCT are: firstly, to examine the effectiveness and cost-utility for FMS patients of MBSR as an add-on to treatment as usual (TAU) versus TAU + the psychoeducational programme FibroQoL, and versus TAU only; secondly, to examine pre-post differences in brain structure and function, as well as levels of specific inflammatory markers in the three study arms and; thirdly, to analyse the role of some psychological variables as mediators of 12-month clinical outcomes.

**Methods:**

Effectiveness, cost-utility, and neurobiological analyses performed alongside a 12-month RCT. The participants will be 180 adult patients with FMS recruited at the Sant Joan de Déu hospital (St. Boi de Llobregat, Spain), randomly allocated to one of the three study arms: TAU + MBSR vs. TAU + FibroQol vs. TAU. A comprehensive assessment to collect functional, quality of life, distress, costs, and psychological variables will be conducted pre-, post-intervention, and at 12-month post-intervention. Fifty per cent of study participants will be evaluated at pre- and post-treatment using Voxel-Based Morphometry, Diffusion Tensor Imaging, pseudo-continuous Arterial Spin Labeling, and resting state fMRI. A cytokine multiplex kit of high-sensitivity will be applied (cytokines IL-6, IL-8, IL-10 + high-sensitivity CRP test).

**Discussion:**

The findings obtained from this RCT will indicate whether MBSR is potentially cost-effective for FMS and contribute to knowledge of any brain and inflammatory changes associated with MBSR in FMS patients. Specifically, we will determine whether there are morphometric and functional changes associated with participation in MBSR in brain regions related to meta-awareness, body awareness, memory consolidation-reconsolidation, emotion regulation and in networks postulated to underpin the sensory-discriminative, cognitive-evaluative and affective-motivational aspects of the pain experience.

**Trial registration:**

NCT02561416. Registered 23 September 2015.

## Background

Fibromyalgia (FMS) is a debilitating syndrome usually diagnosed in women between the ages of 20 and 50 years [1]. It is characterised by multifocal pain, fatigue, disturbed sleep, cognitive problems, and high levels of distress [2]. A survey performed in five European countries indicated that the estimated overall prevalence of FMS is 2.9 % in the general population [3]. Patients with FMS typically present comorbidities with psychiatric disorders such as anxiety (13–63.8 %) and depressive disorders (20–80 %) [4]. In addition, FMS is associated with high direct (medical visits, multiple prescriptions of medications, etc.) and indirect (absenteeism, work loss, etc.) costs in industrialised countries [5]. Among chronic pain conditions, FMS causes the highest rates of unemployment, the highest rate of incapacity benefits claim rate, and the greatest number of days absent from work [6]. FMS represents a great challenge for health professionals because of the lack of optimal treatment options. The effectiveness of pharmacological interventions is generally limited and more ubiquitous effects have been found for non-pharmacological treatments [7].

The Central Nervous System (CNS) seems to play a crucial role in the pathogenesis of FMS [1, 8]. In this regard, structural and functional brain abnormalities in several areas related to pain and stress response regulation (e.g., anterior cingulate cortex, insula, parahippocampal gyrus, prefrontal cortex, somatosensorial cortex) have been observed in patients with FMS. Specifically, significant grey matter reductions in the prefrontal cortex, anterior cingulate cortex and insular cortex have been reported [9]. Such alterations may contribute to the impaired control of pain and abnormal processing of painful stimuli [8]. Alterations in functional connectivity within the brain’s pain inhibitory network; the default-mode network (DMN) and the executive attention network (EAN), as well as greater intrinsic connectivity between the insula and the DMN and EAN were also reported [10, 11]. Furthermore, higher spontaneous pain at the time of the scan was found to be correlated with greater intrinsic connectivity between the insula and both the DMN and the EAN [11]. Moreover, reductions in insula-DMN connectivity were associated with pain reduction in FMS [12], suggesting a key role in the etiology of the disease. Reduced resting connectivity within the somatosensory system and increased connectivity between the DMN and somatosensory processing regions such as S2 have been recently reported [13], which may suggest that a general weakening of sensory integration may be also underlie clinical pain in patients with FMS.

In addition to the aforementioned abnormalities in the CNS, imbalances in inflammatory markers have also been also observed in FMS. Specifically, higher levels of pro-inflammatory cytokines (IL1, IL6, and IL8) and lower levels of anti-inflammatory cytokines (IL4 and IL10) have been reported [14–16]. This cytokine imbalance may produce a chronic inflammatory state in the CNS and the peripheral nervous system, facilitating the sensitisation of peripheral nerves to nociceptive stimuli, increasing hypothalamic-pituitary-adrenal axis activity and the synthesis of prostaglandin and substance P, which lower the pain threshold [14]. Furthermore, cytokines have further effects on the CNS by altering synthesis, reuptake, and release of neurotransmitters involved in the perception, and affective, cognitive and motivational regulation of pain, contributing to structural and functional brain changes and to the perpetuation of pain [17]. Additionally, pro-inflammatory cytokines augment tryptophan metabolism, which may boost affective symptoms in FMS [18–20] and activate glial cells that release a combination of substances into the cerebral spinal fluid that are associated with pain amplification (P substance, glutamate, nerve growth factor, and brain-derived neurotrophic factor) [21].

Contemplatives have pointed out that the practice of meditation reduces the experience of pain by controlling expectations, the nature and orientation of attention towards the experience, and its related emotional response. Mindfulness-based interventions (MBIs) were conceived in the late 1970s from the effort to integrate Buddhist meditation into western psychological practice. In the last decade, there has been growing interest in the effectiveness of MBIs for a range of physical and mental conditions [22], including chronic pain. Veehof et al. [23], in a meta-analysis in chronic pain patients, showed that MBIs have significant effects on pain intensity, depression, anxiety, physical wellbeing, and quality of life. Given that there are no curative treatments available for patients with FMS [1], the putative use of MBIs as coadjuvants of usual care is highly promising.

Bawa and colleagues [24] recently found limited evidence for the effectiveness of MBIs in chronic pain. Their meta-analysis revealed that MBIs have a positive impact on perceived pain control although there was no evidence of a benefit in clinical outcomes. Separate subgroup analysis found evidence of improved physical functioning and quality of life for MBIs versus inactive control conditions. When compared to active control conditions, the effect of MBIs was equivalent to the active comparator. However, results were inconclusive given that the included studies generally involved small samples. In line with these findings, a systematic review of 10 studies [25] indicated that although MBIs provide some significant physical and psychological benefit for patients with FMS, the divergence in the outcomes measured, sample sizes, and data presented failed to establish definitive conclusions about the effectiveness of MBIs. The specific effectiveness of Mindfulness-Based Stress Reduction (MBSR) for FMS patients was evaluated by Lauche and colleagues [26], who found that MBSR improves quality of life and reduces pain in the short term. Nevertheless, further high-quality RCTs are still necessary because of the considerable methodological limitations of the meta-analysed studies (e.g., absence of randomization, high attrition rates, or small sample sizes).

There is a great amount of evidence of structural changes in experienced meditators compared to individuals without meditative experience [27, 28]. These changes would be indicative of increases in meta-awareness (frontopolar cortex), exteroceptive and interoceptive body awareness (sensory cortices and insula), memory consolidation and reconsolidation (hippocampus), self and emotion regulation (anterior, mid cingulate and orbitofrontal cortices), and intra- and interhemispheric communication (superior longitudinal fasciculus, corpus callosum) associated with meditation. Structural changes in specific brain areas (e.g., hippocampus, posterior cingulate cortex, the temporo-parietal junction, and cerebellum) have been reported after a MBSR intervention [29].

Significant differences in brain function have been observed between meditators and non-meditators. In this regard, Brewer et al. [30] found reduced activation of two main DMN nodes (posterior cingulate cortex and medial prefrontal cortex) and activations of the medial prefrontal cortex, insula, and temporal lobes during meditation in individuals with meditative experience, showing a differential pattern of functional connectivity both during resting and when practicing mindfulness. Similarly, Jang et al. [31] reported greater functional connectivity (at rest) in some areas of the DMN (i.e., the medial prefrontal cortex) in individuals with meditative experience, suggesting that meditation practice would be associated with functional changes in DMN areas even when not practicing meditation. Furthermore, functional brain changes (e.g., increases in left frontal activation, higher activity in insula, secondary somatosensorial cortex, anterior cingulate cortex, lower activity in right amygdala and in several DMN regions) have been observed after standard MBSR [32]. All the brain changes following mindfulness training are associated with increased learning and memory processes, emotion regulation, self-referential processing, and perspective taking, an augmented experiential, present-focused mode of self-reference, higher interoceptive awareness, more accurate processing of exteroceptive sensory events, higher attentional control and reduced conceptual processing [29, 32, 33]. Interestingly, mindfulness training seems to impact on pain experience as significantly lower pain unpleasantness and intensity ratings (compared to resting state) were found after a brief mindfulness training session when meditating in the presence of painful stimulation [34]. In this study, reductions in pain intensity ratings were found to be associated with increased activity in areas involved in the cognitive and affective regulation of nociceptive processing (anterior cingulate cortex and insula) and reductions in pain unpleasantness ratings were associated with increased activity in brain areas (orbitofrontal cortex) involved in reframing the contextual evaluation of sensory events and diminished thalamic activity, which may reflect a change in the interaction between afferent input and executive-order brain areas.

Improvements in immune function after mindfulness training have also been reported. In this regard, reduced psychophysiological stress and inflammatory responses (levels of the pro-inflammatory cytokine IL-6, C reactive protein, or in the expression of pro-inflammatory genes related to NF-κB factor) have been reported after mindfulness training [35–37]. For instance, there is some evidence of beneficial effects of mindfulness training on cell-mediated immunity in patients with cancer [38], and HIV [35, 39]. Studies with larger samples and more adequate methodologies (e.g., using more rigorous control groups, longer follow-ups) are needed to better ascertain the effects of MBSR on inflammatory processes. A recent meta-analysis [40] examined the impact of mind-body treatments (including meditation, Tai Chi, Qi Gong, and Yoga) on inflammatory markers, finding that when all results from healthy and heterogeneous clinical samples were pooled, there was some evidence supporting an anti-inflammatory effect of mind-body treatments.

There is currently a total absence of empirical evidence regarding the cost-effectiveness of MBIs for FMS syndrome. Worldwide, mindfulness research is rapidly expanding and being applied in different contexts, and there has been a call for more health economics research. Bearing in mind that costs are of crucial importance for policy-makers, who usually consider as first-choice treatment those interventions with the lowest cost per quality-adjusted life-year (QALY), economic evaluations of MBIs in FMS should be carried out to ensure (if cost-effective) their implementation in healthcare systems. Moreover, the evidence for mindfulness as the causal factor in structural and functional brain changes [27, 32] and the mechanistic effects of inflammatory markers on the therapeutic effects of mindfulness remain tenuous, so further work is needed to gain a deeper understanding of how mindfulness actually works.

Taking these issues into consideration the aim of this 12-month randomised, controlled trial (RCT) is three-fold: firstly, to examine the effectiveness and cost-utility for FMS patients of MBSR as an add-on to treatment as usual (TAU) versus a psychoeducational programme (FibroQoL) that recently that has been shown to be a cost-effective adjuvant to TAU [41]. Secondly, to examine pre-post neurobiological changes in brain structure and function, as well as in levels of some pro- and anti-inflammatory markers in the three study arms (TAU vs TAU + MBSR vs TAU + FibroQoL). Thirdly, to analyse the role of specific process variables (facets of mindfulness, pain catastrophism, psychological inflexibility, and self-compassion) as mediators of long-term clinical improvement.

## Methods

### Study design

This RCT protocol was developed following the Standard Protocol Items: Recommendations for Interventional Trials (SPIRIT) [42] and was recorded in the ClinicalTrials.gov trial register in September 2015 (NCT02561416). We designed a 12-month, parallel group, randomised (using a computer-generated randomisation list), single-blind, controlled trial (RCT) with three treatment arms. The Consolidated Standards of Reporting Trials 2010 (CONSORT) [43] and the Consolidated Health Economic Evaluation Reporting Standards (CHEERS) [44] will be followed. The three treatment arms are:TAU + MBSRTAU + FibroQoLTAU

Patients from the three study arms will receive TAU; given that MBSR and FibroQoL were originally developed as complements to usual care, not as substitutes for it. Fifty percent of the participants in each study arm will undergo neurobiological evaluations (neuroimaging and inflammatory markers).

### Participants

A total of 180 FMS patients will be recruited from the Rheumatology service at Sant Joan de Déu Hospital (St. Boi de Llobregat, Spain). Sample size is established on the basis of a previous meta-analysis of controlled MBSR trials [45] in which a mean effect size of *d* = 0.53 was found. This effect size results in 1-b = 0.89 (alpha = 0.05) for *N* = 60 patients per group (180 patients overall). With 20 % maximal attrition, the power remains 1-b = 0.82. The estimated sample size for the study of biomarkers (neuroimaging and cytokines) was 30 participants per condition, this sample size is considered adequate given that approximately 20–40 participants (in between-group designs) are necessary to detect a change of 15 % in cerebral blood flow in regions of interest (ROI) by means of pseudo-continuous Arterial Spin Labeling (pCASL) [46].

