## Discussion

The study described here will evaluate, for the first time, the cost-utility of MBSR for FMS patients compared with usual care and with an empirically-validated intervention (FibroQol) which proved to be cost-effective in such patients in a high-quality RCT [41]. Therefore, this is a 3-armed RCT in which we include an active control condition (psycho-education) that permits us to control the “frustrebo response” (disappointment among control participants at not receiving treatment) associated with waiting-list and TAU conditions [92]. The RCT was designed following the CONSORT recommendations, the economic evaluation was planned following the updated ISPOR core recommendations for cost-effectiveness analyses alongside RCTs, the sample size in each study arm is sufficiently large and the follow-up period is sufficiently long to capture important costs and outcomes. If our trial results are sufficiently robust, MBSR programmes might be delivered as part of a strategic, coherent or appropriately resourced approach for patients with FMS in the healthcare context [80, 93]. According to Gotlink et al. [80], “*further research should also look more into the mechanisms whereby these therapies (MBSR-MBCT) are efficacious*”. In the present RCT, we are not only interested in the clinical effects of MBSR at long-term, but also in the “process” psychological variables and neurobiological changes that contribute to them, which is a current source of interest and debate in the scientific literature [89, 94].

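### The single power figure rests on a general d = 0.53 and names no contrast; for MBSR versus FibroQoL that effect is unsupported, so the stated 0.89 / 0.82 should not be read as covering it

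*Protocol article*

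**What the plan says.** The sample-size paragraph (Protocol article, Methods, Participants) uses one effect input: "Sample size is established on the basis of a previous meta-analysis of controlled MBSR trials", in which a "mean effect size of *d* = 0.53 was found". The type of control, the outcome and the population of those trials are not given. The power statement follows: "This effect size results in 1-b = 0.89 (alpha = 0.05) for *N* = 60 patients per group (180 patients overall". After dropout: "With 20 % maximal attrition, the power remains 1-b = 0.82". No contrast or comparator is attached to either figure.

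Elsewhere the article gives these facts:
- **Aims.** The Abstract compares MBSR with both FibroQoL and TAU only. The aims paragraph that closes the Background names only FibroQoL as comparator in the first aim, describing it as a programme "that recently that has been shown to be a cost-effective adjuvant to TAU".
- **Nature of FibroQoL.** The note to Table 2 says the programme was cut to eight sessions so that it is structurally equivalent to MBSR and matches it in non-specific factors. The Discussion calls it empirically validated.
- **Evidence against active controls.** The Background reports a meta-analysis of mindfulness interventions (MBIs) in chronic pain, with better physical functioning and quality of life than inactive controls. It continues: "When compared to active control conditions, the effect of MBIs was equivalent to the active comparator". The next sentence adds that "results were inconclusive given that the included studies generally involved small samples".
- **Analysis.** The section on clinical efficacy plans Bonferroni-adjusted pairwise contrasts, and Cohen's d with 95 % confidence intervals.

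**The concern.** A reader who finds one power figure and a first aim that includes FibroQoL is likely to take the figure as covering MBSR versus FibroQoL. That contrast isolates what is specific to mindfulness, because FibroQoL was edited to share the non-specific ingredients. It is also the contrast for which a mean effect from controlled MBSR trials in general is least likely to apply.

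If the true advantage over FibroQoL is small, a non-significant result is the probable outcome. Set beside a stated power of 0.82 to 0.89, that result could be taken as evidence of no difference, which a trial of this size could not supply. The issue is the effect input. It remains whatever view is taken of the sidedness of the test or of multiplicity.

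**Working it through.** **Inputs.** From Participants: d = 0.53, alpha = 0.05 (sidedness not stated), n = 60 per arm, and 20 % attrition, so 60 × 0.8 = 48 per arm. From the clinical efficacy section: Bonferroni over pairwise contrasts. The number of contrasts is not given; three is assumed, so alpha = 0.05/3 = 0.0167. The documents give no d for MBSR versus FibroQoL; 0.2 to 0.4 is an assumption.

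**Formula.** Two-sample comparison of means with noncentrality d × √(n/2). In the normal approximation, power = Φ(d√(n/2) − z), with z = 1.645 (one-sided 5 %) or 1.960 (two-sided 5 %). The t results below use the noncentral t with 2n − 2 degrees of freedom.

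**Step 1: reproduce the stated figures.** For d = 0.53 the noncentrality is 0.53 × √30 = 2.903 at n = 60 and 0.53 × √24 = 2.596 at n = 48.
- One-sided 5 %: Φ(2.903 − 1.645) = 0.896 and Φ(2.596 − 1.645) = 0.829; by t, 0.893 and 0.825. This matches 0.89 and 0.82.
- Two-sided 5 %: Φ(2.903 − 1.960) = 0.827 and Φ(2.596 − 1.960) = 0.738; by t, 0.821 and 0.729. This does not match.
- A three-group omnibus ANOVA with f = 0.53/2 = 0.265 gives 0.894 and 0.811. This is close, but it is not a test of MBSR versus FibroQoL.

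The one-sided basis is thus inferred from the fit; the article does not state it.

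**Step 2: can 0.53 serve both contrasts?** On a common standard deviation,

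d(MBSR − FibroQoL) = d(MBSR − TAU) − d(FibroQoL − TAU).

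Both MBSR contrasts can equal 0.53 only if d(FibroQoL − TAU) = 0, that is, if FibroQoL adds nothing to usual care on the outcome. The article's description of FibroQoL as a validated adjuvant points the other way.

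**Step 3: power over the assumed range (t test).**

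| d | One-sided 5 %, n = 60 / 48 | Two-sided 5 %, n = 60 / 48 | Two-sided 0.05/3, n = 60 / 48 |
|---|---|---|---|
| 0.2 | 0.29 / 0.25 | 0.19 / 0.16 | 0.10 / 0.08 |
| 0.3 | 0.50 / 0.43 | 0.37 / 0.31 | 0.22 / 0.17 |
| 0.4 | 0.70 / 0.62 | 0.58 / 0.49 | 0.41 / 0.32 |
| 0.53 | 0.89 / 0.82 | 0.82 / 0.73 | 0.68 / 0.56 |

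Even on the one-sided basis that reproduces the article, d = 0.4 gives 0.703 against 0.893 at n = 60, a gap of 0.19.

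**Step 4: smallest d with 80 % power.** This needs no assumed d. Normal approximation, two-sided 5 %: (1.960 + 0.842) × √(2/n) = 0.51 at n = 60 and 0.57 at n = 48. The t solution is 0.516 and 0.578. At alpha = 0.05/3 it is 0.598 and 0.671.

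**The case against.** Several points on the other side are sound.

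- **Scope of the claim.** A reader might infer that the article claims 0.89 for every contrast. It does not say so: the paragraph names none, and the Abstract lists TAU only as a comparator too. What stands is that the figure has no stated scope.
- **Strength of the background evidence.** A reader might infer that the Background contradicts d = 0.53 against FibroQoL. It does not. The result concerns mindfulness interventions in general, in chronic pain in general, and the article itself calls it inconclusive. It leaves 0.53 unsupported for this contrast, not disproved. The subtraction in step 2 does not depend on it, although cost-effectiveness is not itself an effect on the FIQR.
- **Unknown source mix.** The article does not say whether the trials behind 0.53 used active controls, so the effect cannot be assigned to the TAU contrast by default either.
- **The Discussion's remark.** The phrase "the sample size in each study arm is sufficiently large" is tempting as a power claim. It is a general statement about capturing costs and outcomes and follows the economic evaluation, so nothing rests on it here.
- **Interpretation.** The article nowhere says that a null FibroQoL result will be reported as equivalence, and effect sizes with confidence intervals are already planned. The risk lies in how readers might use the power figure, not in a stated intention.

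The power arithmetic is correct for d = 0.53 with a one-sided test. What remains is that one unscoped figure stands beside two comparators for which a common effect is implausible on the article's own account.

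**Conclusion.** The point holds in a limited form. The article does not justify d = 0.53 for MBSR versus FibroQoL, so 0.89 / 0.82 should not be read as the power of that contrast. The firm result is the detectable difference: with 80 % power and a two-sided 5 % test, about 0.52 at 60 and 0.58 at 48 per arm, or about 0.60 and 0.67 if Bonferroni covers three contrasts. The contrast therefore reaches 80 % power only if MBSR exceeds a matched active programme by roughly the whole mean effect quoted for controlled MBSR trials, or more.

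The power range of 0.19 to 0.58 (60 per arm) or 0.16 to 0.49 (48 per arm) is an illustration that depends on an assumed d of 0.2 to 0.4. It does not show that the true effect is that small. All figures assume a simple two-group comparison with a common standard deviation; the planned mixed model could shift them.

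**What to change.** Amend the sample-size paragraph under Participants:

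1. State which contrast d = 0.53 is meant for, and why that source applies to it.
2. For MBSR versus FibroQoL, replace the power claim with the smallest difference detectable with 80 % power on the planned test, using the figures in the verdict. Give the power over an assumed d of 0.2 to 0.4 as illustration, labelled as an assumption.
3. Put any power kept for MBSR versus TAU on the same two-sided, multiplicity-adjusted basis. Do not carry over 0.89 / 0.82: at d = 0.53 the two-sided values are 0.82 / 0.73, or 0.68 / 0.56 with Bonferroni over three contrasts.
4. State that a non-significant MBSR versus FibroQoL result will be interpreted from the confidence interval already planned in the clinical efficacy section, and not as equivalence.

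The cost is wording only: no extra patients, no change of design. The downside is a less favourable stated power.

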#### Analysis of clinical efficacy

To assess treatment effects, we will perform Intention-to-Treat analyses, which will include all participants who undergo random allocation, using multiple imputation to replace missing values.

To study the differences in the primary outcome and in each of the secondary outcomes between groups, linear mixed-effects models [85] will be prepared using Restricted Maximum Likelihood to estimate the parameters. Comparisons amongst treatment groups at post-treatment and at 12-month follow-up will be computed with estimates derived from the linear mixed-effect models (use of the Bonferroni method to adjust the significance level of the pairwise contrasts). Calculations of between-groups effect sizes using Cohen’s *d* with its 95 % confidence interval will be based on the pooled standard deviation at baseline. Finally, to make the findings from the present RCT meaningful to clinicians, the number-needed-to-treat (NNT) [86] in the MBSR condition will be reported. Taking the Luciano et al. [87] NNT approach as our reference, we dichotomise participants into responders or non-responders using three separate cut-off criteria: (a) ≥ 20 % reduction on the FIQR total score from baseline to post-treatment; (b) ≥ 50 % reduction on the FIQR total score from baseline to post-treatment; and (c) number of patients crossing a cut-off point (reaching no worse than mild functional impairment; FIQR total score < 39).

Given that some pharmacological treatments may interfere with cytokine levels [88], differences in cytokine levels between patients taking vs. not taking antidepressants will be evaluated.

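### The stated power of 0.89 (0.82 after attrition) is not the power of the Bonferroni-adjusted pairwise contrasts that the protocol plans

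*Protocol article*

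**What the plan says.** Under Participants, the protocol article takes its effect size from a meta-analysis of controlled MBSR trials, "in which a mean effect size of *d* = 0.53 was found". It then states the power: "This effect size results in 1-b = 0.89 (alpha = 0.05", for "60 patients per group (180 patients overall". For losses it adds: "20 % maximal attrition, the power remains 1-b = 0.82". The paragraph does not say whether the test is one-sided or two-sided, mentions no adjustment for three arms, and does not say which pair of arms the effect size refers to.

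Under Analysis of clinical efficacy, the primary outcome (FIQR) is analysed with linear mixed-effects models. Treatment groups are compared at post-treatment and at 12 months by contrasts from the model, with "use of the Bonferroni method to adjust the significance level of the pairwise contrasts". Cohen's d is to be reported with a 95% confidence interval. Sidedness is not stated here either.

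**The concern.** A power figure describes a particular test. Here the sample size paragraph and the analysis section describe different tests. Three arms give three pairwise contrasts, so Bonferroni reduces the per-contrast level from 0.05 to 0.05/3 = 0.0167 at a given time point. The sample size paragraph uses 0.05. In addition, 0.89 is higher than the usual two-sided calculation gives for d = 0.53 and 60 per arm, even before any adjustment.

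The power statement is the trial's main quantitative justification for 180 patients. A reader would take from it a chance of about 9 in 10 (8 in 10 after dropout) of detecting d = 0.53 in the planned comparisons. On the article's own inputs that is not what the planned contrasts deliver, unless an assumption is added that the article does not make.

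**Working it through.** **Inputs**
- d = 0.53; alpha = 0.05; n = 60 per arm; 20% attrition, so 60 × 0.80 = 48 per arm (Participants).
- Three arms, hence three pairwise contrasts per time point (Study design).
- Bonferroni on the pairwise contrasts: 0.05/3 = 0.0167 (Analysis of clinical efficacy).
- Sidedness and the correlation between baseline and later FIQR are not given. Both are treated as assumptions.

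**Formula.** For a two-sample t-test with n per arm, the noncentrality is d × √(n/2), with 2n − 2 degrees of freedom. Power is the probability that this noncentral t exceeds the critical value.
- n = 60: 0.53 × √30 = 2.903, 118 df.
- n = 48: 0.53 × √24 = 2.596, 94 df.

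**Step 1. Reproducing the stated 0.89 / 0.82**
- One-sided 0.05, unadjusted (critical t 1.658 / 1.661): 0.893 / 0.825. Both agree with the text.
- Two-sided 0.05, unadjusted (critical t 1.980 / 1.986): 0.821 / 0.729. Neither agrees.
- Omnibus F over three groups with f = d/2 = 0.265: 0.894 / 0.811. The first agrees and the second is 0.01 low. However, f = d/2 is the two-group conversion. With two arms equal and one shifted by 0.53, power is 0.854 / 0.761; with evenly spaced means over a range of 0.53, it is 0.734 / 0.628.

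The stated power after attrition, 0.82, equals the ordinary two-sided power before any attrition (0.821).

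**Step 2. Power of the planned contrasts, Bonferroni over three at one time point, no gain from baseline**

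| Test | n = 60 | n = 48 |
|---|---|---|
| Two-sided, 0.0167 (critical t 2.429 / 2.438) | 0.68 | 0.56 |
| One-sided, 0.0167 (critical t 2.153 / 2.160) | 0.77 | 0.67 |
| Stated in the article | 0.89 | 0.82 |

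The two-sided gap is 0.89 − 0.68 = 0.21 and 0.82 − 0.56 = 0.26. The one-sided gap is 0.12 and 0.15.

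**Step 3. Possible gain from the baseline score.** If the model works like ANCOVA and baseline and follow-up FIQR correlate at r, the effective effect size is 0.53/√(1 − r²). At r = 0.5, for example, this is 0.53/0.866 = 0.612. Two-sided power at 0.0167 is then:

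| Assumed r | n = 60 | n = 48 |
|---|---|---|
| 0.3 | 0.73 | 0.61 |
| 0.5 | 0.82 | 0.71 |
| 0.6 | 0.88 | 0.79 |
| 0.65 | 0.92 | 0.83 |

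Both stated figures are reached only with an assumed correlation of roughly 0.65.

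**The case against.** The strongest defence is that the planned analysis is a mixed model on repeated FIQR scores, not a raw two-sample t-test, so 0.68 and 0.56 may be too pessimistic. This stands in part. At r = 0.65 the adjusted contrasts would reach the stated power, so a reader should not conclude that the trial necessarily falls short; the article does not settle its true power. What the defence does not rescue is the power statement itself, which gives no correlation and claims no gain from baseline.

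Second, two-sided testing is inferred. The 95% interval in the analysis section belongs to Cohen's d and does not fix the sidedness of the contrasts. This is correct, but one-sided Bonferroni contrasts still give only 0.77 and 0.67.

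Third, the authors may not have used a one-sided t-test at all; an omnibus F with f = d/2 comes close. The route therefore cannot be stated as fact. Neither route is the planned pairwise test.

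Fourth, a journal article condenses the full protocol. But this is not an omission: the article prints specific power values and a specific testing rule, and they do not agree.

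Two further inferences are tempting and not supported. The Background says of mindfulness interventions, "When compared to active control conditions, the effect of MBIs was equivalent to the active comparator", from which one might conclude that the FibroQoL contrast is hopeless or that a null result there would be taken as equivalence. The Background itself goes on to call those results inconclusive because of small samples, and no equivalence claim is planned. The Discussion's phrase "the sample size in each study arm is sufficiently large" might be read as a power claim, but its sentence is about capturing important costs and outcomes.

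**Conclusion.** The stated 0.89 and 0.82 are wrong as a description of the planned analysis. For d = 0.53 they agree with an unadjusted one-sided test. The Bonferroni-adjusted contrasts have power 0.68 (60 per arm) and 0.56 (48 per arm) if two-sided, or 0.77 and 0.67 if one-sided. These values assume three contrasts at one time point, equal arms and no gain from baseline. The mismatch holds under either choice of sidedness. Only an assumed baseline correlation of about 0.65, which the article does not invoke, would bring two-sided adjusted power up to both stated values. The finding concerns the power statement and is not proof that the trial is underpowered.

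A smaller point belongs with it. One d = 0.53 is applied without distinction to the comparison with TAU and to the comparison with FibroQoL, an active programme built to match MBSR in non-specific factors.

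**What to change.** In the Participants section:
- State whether the tests are one-sided or two-sided.
- Replace 0.89 and 0.82 with the power of the Bonferroni-adjusted contrasts. If two-sided at 0.0167, this is 0.68 with 60 and 0.56 with 48 per arm for d = 0.53.
- If a gain from the baseline FIQR is to be claimed, give the assumed correlation and its source, and show power over a range such as that in Step 3.
- Say that the same d = 0.53 is used for both the TAU and the FibroQoL comparison.

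The cost is a rewritten paragraph and a less favourable stated figure. The design, the analysis section and the number of patients stay as they are.
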